The peptides were dissolved in liquid chromatography's mobile phase A and separated using the EASY-nLC 1200 ultra-high performance liquid phase system (ThermoFisher Scientific). Mobile phase A was an aqueous solution with 0.1 percent formic acid and 2% acetonitrile, while mobile phase B was an aqueous solution with 0.1 percent formic acid and 90% acetonitrile. The setting for liquid phase gradient: 0-114 minutes, 4 percent 33 percent phase B; 114-117 minutes, 33 percent 80 percent phase B; 117-120 minutes, 80 percent phase B. The flow rate was kept constant at 500 nL/min. The peptides were separated using an ultra-high performance liquid system, then injected into an NSI ion source for ionization before being evaluated in Q ExactiveTM HF-X (ThermoFisher Scientific).

The liquid phase parameters remained unchanged from when the library was created. Peptides were isolated using an ultrahigh performance liquid chromatography system and evaluated using Q ExactiveTM HF-X mass spectrometry. The high-resolution Orbitrap was used to detect and analyze peptide precursor ions and their secondary fragments. The primary mass spectrometer's scanning range was set at 385-1200 m/z, and the scanning resolution was set to 120000; the secondary scanning resolution was set to 15000. The data acquisition mode employed the data-independent scanning (DIA) program, in which peptide ions were fragmented in the HCD collision cell utilizing 27 percent of the fragmentation energy, followed by secondary mass spectrometry analysis. The secondary spectrum's automatic gain control (AGC) was set to 5E5, and the fixed initial mass was set to 200 m/z.

Protein Annotation in LC-MS/MS

MaxQuant search engine (v.1.6.15.0) was used to process the generated MS/MS data. Tandem mass spectra were compared to the human SwissProt database (20422 entries), which was concatenated with the reverse decoy database. Trypsin/P was chosen as the cleavage enzyme, with up to two missed cleavages permitted. In the first search, the mass tolerance for precursor ions was set to 20 ppm and 5 ppm in the main search, while the mass tolerance for fragment ions was set to 0.02 Da. FDR was adjusted to < 1%.

Proteomics Assays Data Analysis

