Data on protein expressions came from two distinct groups (Group A: The FOLFOX4-ATRA group and Group B: the FOLFOX4-placebo group). Samples from the baseline (before treatment) and time point (after treatment) measurements formed 4 experimental subgroups (Subgroup A – before, Subgroup A – after, Subgroup B – before, Subgroup B – after). Samples from patients with PD, SD, PR, and CR were measured for each subgroup.

All protein expression values were normalized by calculating the relative abundance of each protein in each sample. Analyses of differential protein expression were conducted by fitting linear mixed models (LMM) with the lme4 R package25 and proteins whose expression levels were undetectable in more than 40 samples were not analysed The protein expression was a response variable (y), while the explanatory variables were treatment response (PD, SD, PR, and CR), time point (pre and post treatment), and treatment group (Group A and Group B) used as fixed effects. The patient ID was used as a random effect to allow us to account for the samples being paired (same samples measured in the pre and post therapy). To test for differences between different treatment responders to FOLFOX4-ATRA therapy, the generalized linear hypothesis (glht) function from the multcomp R package26 was utilized to test for the following three contrasts: (1) differences in protein expressions between patients with PD, SD, PR, and CR before therapy in Group A, (2) similar differences in Group B, and (3) any interaction when comparing differences between Group A and Group B. To test for the differences in the pre and post FOLFOX4-ATRA therapy, the following three contrasts were absotested: (1) differences in protein expressions in pre and post therapy in Group A, (2) differences in pre and post therapy in Group B, and (3) any interaction when comparing the differences between Groups A and B. The resulting p-values were adjusted using the FDR method to account for multiple comparisons.

Figure. S1.

[figure not shown]

Typical patient 1: A, C: Pulmonary metastasis before treatment; B, D: The lesions disappeared after FOLFOX4-ATRA

Figure. S2.

[figure not shown]

Typical patient 1: A, C: Abdominal metastasis before treatment; B, D: The lesions disappeared after FOLFOX4-ATRA.

Figure. S3.

[figure not shown]

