Proteins that differed significantly between FOLFOX4-ATRA responders and non-responders prior to treatment (P value < 0.05). **A,** Heat map of significantly distinct proteins illustrating the difference between group A and group B patients for two-way comparisons between PD, SD, PR, CR, and RE (CR+PR), as well as the change in their differential expression in the pre and post therapy. The color of the heat map represents the regression coefficient in the linear regression test. **B,** the enrichment of Gene Ontology for different protein modules. **C,** The enrichment of KEGG pathways for different protein modules.

**CR_up:** SOD3, SERPINF2, AZGP1, APOF, PTPRM, FCN3, ALB, CACNA2D1, BTD, KRT81, TTR, SSC5D, PI16, GP5, IGKV1D−33. **RE_down**: FABP1, IGLV5−39, KRT6C, IGKV2D−29, IGLV5−45, ATXN7L2, VCAN, SLC4A1, PLGLA, IGLC7, MEGF8, FCGR3A, LRRC4. **PR_up**: F8, GSS, IGHV1−69, IGHV5−10−1, C4A, RNASE4, FBLN5, ALDOB, ANXA3. **SD_down**: UMOD, ABI3BP, AFM, ERAP2, IGHV3−38, IGLV2−18, TGFB1, ADARB1, IGLV7−46, WRAP73, IGLV3−19, ICAM3, IGLV1−51, F12, PSAP, PFN1, MST1L, IGLL5, IGKV3−20, IGHV3−7, IGHG2, FCGR3B, ATRN, DBH. **SD_up**: APCS, SPARCL1, PRG4, CFHR2, IGF2R, ASGR2, ITIH3, RELN, IGHD, ITIH4, ORM1, SERPINA3, SAA4, HPD, AGT, F11.

Figure. S4.

[figure not shown]

Proteins that differed significantly between pre and post FOLFOX4-ATRA treatment (P value < 0.05). A, Heat map of significantly distinct proteins illustrating the difference between group A and group B patients for two-way comparisons between PD, SD, PR, CR, and RE (CR+PR), as well as the change in their differential expression in the pre and post therapy. The color of the heat map represents the regression coefficient in the linear regression test. B, the enrichment of Gene Ontology for different protein modules. C, The enrichment of KEGG pathways for different protein modules.

**Treat_RE_up:** TPI1, CILP, IGHG3, TMEM198, A1BG, SELENBP1, CFHR4, PROCR, VCAM1, FCGR2A, LYVE1, APOC1, KNG1, MEGF8. **Treat_RE_down:** FLNA, IGHV2−70D, F8, IGF1, F12. **Treat_SD_up:** PLTP, ALCAM, ADGRG6, PLA2G7, COL18A1, OLFM1, FUCA1, F7, COL3A1, CDH2, APOC4, CD163, SPP2, ATRN, B4GAT1. **Treat_SD_down:** APCS, SAA4, HPD, C6, C8A, F9, ITIH4. **Treat_PD_up:** SLC4A1, PLS1, PFN1, PDIA3, IGLV1−51, IGKV3D−20, ATXN7L2, HBG2.

Table S1.

Univariate and Multivariable Analysis of OS

| Variables |  | | Univariate Analysis | |  | | Multivariable Analysis | |
| --- | --- | --- | --- | --- | --- | --- | --- | --- |

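### The proteomics methods promise FDR-adjusted p-values, but the Figure S3 and S4 legends call proteins significant at a plain P < 0.05; the two must be reconciled.

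*Combined protocol and SAP*

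**What the plan says.** The subsection Proteomics Assays Data Analysis (supplementary Materials and Methods) fits a linear mixed model per protein. It tests two sets of contrasts:

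- differences between PD, SD, PR and CR before therapy, in Group A, in Group B, and the interaction;
- pre/post differences in Group A, in Group B, and the interaction.

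It closes with: "The resulting p-values were adjusted using the FDR method to account for multiple comparisons". No procedure, cut-off or family is named. On how many proteins entered, it gives only a filter: "proteins whose expression levels were undetectable in more than 40 samples were not analysed".

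The legends define significance differently. Figure S3: "Proteins that differed significantly between FOLFOX4-ATRA responders and non-responders prior to treatment (P value < 0.05". Figure S4: "Proteins that differed significantly between pre and post FOLFOX4-ATRA treatment (P value < 0.05". Both describe heat maps of "two-way comparisons between PD, SD, PR, CR, and RE (CR+PR"), and both use the selected proteins for named modules and for GO and KEGG enrichment.

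One numerical FDR level does appear, under Protein Annotation in LC-MS/MS ("FDR was adjusted to < 1" per cent). It governs the identification of spectra in the database search, not the differential-expression tests.

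**The concern.** A reader cannot tell which rule put a protein on the lists. The methods describe multiplicity control, while the legends state a threshold that, read literally, has none. The modules and the enrichment in panels B and C start from these lists, so any false positives at the selection step carry through to the pathway results.

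The mismatch goes beyond one number. The legends use a pooled responder class, RE, and the S4 modules split pre/post change by response (RE, SD, PD). The methods list neither. So even if an adjustment was made, it is unclear whether it covered every comparison behind the figures.

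**Working it through.** The documents give no number of proteins tested, no expected false-positive count and no FDR level for these tests, so there is no stated figure to reproduce. The check asks how much the two readings of the threshold differ.

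**Inputs from the documents**

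- Threshold: 0.05 (both legends).
- Proteins listed in S3: 15 + 13 + 9 + 24 + 16 = 77.
- Proteins listed in S4: 14 + 5 + 15 + 7 + 8 = 49.
- Twelve names appear in both, so 77 + 49 − 12 = 114 are distinct.
- Number tested, m: not stated. It cannot be smaller than the number listed, so 77 is a safe floor. The SwissProt count of 20,422 is the search space, not m.

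**Expected false positives if P is unadjusted and nothing differs.** The expectation is 0.05 × m per contrast, whether or not proteins are correlated.

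- m = 77: 3.85
- m = 200 (assumed): 10
- m = 1,500 (assumed): 75

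**Chance of at least one hit, one test per protein.** Under independence this is 1 − 0.95^m, so 1 − 0.95^77 = 98.1% and 1 − 0.95^114 = 99.7%. With equally correlated test statistics (4,000 simulated data sets per row), it falls. The last column applies Benjamini-Hochberg at an assumed q of 0.05 to the same null data.

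| Correlation | Unadjusted, m = 77 | Unadjusted, m = 114 | Unadjusted, m = 1,000 | BH, m = 77 |
| --- | --- | --- | --- | --- |
| 0 | 98% | 99.7% | 100% | 5.6% |
| 0.3 | 90% | 96% | 100% | 4.6% |
| 0.5 | 72% | 81% | 99.9% | 3.3% |
| 0.8 | 33% | 38% | 58% | 1.8% |

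The 5.6% is simulation noise around a true 5%.

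**Could chance produce a list as long as S3?** This depends on m and on how many contrasts could admit a protein.

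- One test each: 77 / 0.05 = 1,540 null proteins would be needed to give 77 hits on average.
- Any of the six pairwise contrasts among four equal response groups: a null protein is flagged with probability 0.204 (simulated), so 77 / 0.204 = 377 proteins would be enough.
- Adding RE versus PD and RE versus SD, under three assumed sets of response-group sizes, leaves the flagging probability at 20.2% to 20.6%.

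These simulations use simple normal contrasts, not the mixed model in the methods. The required m therefore runs from about 380 to about 1,540, depending on a selection rule that the legends do not spell out.

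**The case against.** The strongest reply is that neither legend says nominal, raw or unadjusted. The methods end by saying that the p-values were adjusted, and the legends follow in the same supplement, so P value may be shorthand for the adjusted value. The figure panels are not available to me, and a colour key or axis label could say so. On that reading the lists have roughly the promised control and only the labelling is at fault. This stands as a possibility. It does not remove the conflict in the text, because the methods give no cut-off or family and the legends add comparisons that the methods do not mention.

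Second, proteins are correlated. Many of those listed are immunoglobulin chains, and all values are relative abundances. This also stands: at a correlation of 0.8 the chance of any false hit with 77 proteins is 33%, not 98%. The expected count of 0.05 × m does not change.

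Third, the legends attach the threshold to responders versus non-responders (S3) and to pre versus post (S4). The two-way comparisons are described as what the heat map displays, so selection on any pairwise contrast is an inference. Hence the wide range for m above.

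Fourth, neither the protocol objectives and endpoints nor the SAP hypotheses and outcomes mention proteomics. That is correct and limits the weight of the point.

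**Conclusion.** The stated selection rule and the stated multiplicity control conflict. The unadjusted reading is the natural one, but it is not established. If it is right, the 77 and 49 listed proteins and the enrichment lack the error control that the methods describe. The size is then 0.05 × m expected false positives per contrast under no effect, and a 33% to 98% chance of at least one hit at m = 77 as the correlation falls from 0.8 to 0. The comparable chance with Benjamini-Hochberg is about 2% to 5%. These figures rest on one test per protein, an assumed m (77 as a floor, 200 to 1,500 as a range) and an assumed q of 0.05.

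A reader might go further and infer that a responder signature would appear almost surely even if no protein differed, or that lists of 77 and 49 are what chance produces. The documents do not support either. The first needs an unadjusted P and limited correlation, and it treats a single passing protein as a signature. The second needs m and the selection contrasts, which are not stated; chance could give lists of this length, but that is not shown. Nor does the supplied text claim that baseline proteins mark responders; it lists proteins and modules.

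The analysis is exploratory. The point affects how the figures may be read, not any trial endpoint.

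**What to change.** State one rule in the methods and in both legends. Select proteins for the heat maps, modules and GO/KEGG enrichment on FDR-adjusted p < 0.05. Name the procedure, the number of proteins tested and the family, and include the RE and response-split pre/post contrasts in it. FDR control per contrast or pooled over contrasts is acceptable, provided it is stated.

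If unadjusted P is kept for display, label the lists nominal and exploratory, drop the claim of significance, and print the number of proteins tested with the number expected by chance.

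If adjusted values were already used, print 'FDR-adjusted P < 0.05' in both legends and add the missing contrasts to the methods.

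The cost is small: at most re-filtering existing results, adjusting any contrast not yet covered, rerunning the enrichment and rewording two legends. No new data are needed. The downside is that the lists may become shorter, or empty.

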# Introduction and Study Rationale

Hepatocellular carcinoma (HCC) is the fifth most common cancer in men, the eighth in women, and the third most frequent cause of cancer-related death worldwide, with more than 626,000 new cases per year^1^. The geographic distribution is not uniform across the world: approximately 80% of cases arise in Asia and Africa where HCC incidence is 30-120/100,000 in males, 9-30/100,000 in females. The incidence in Europe and North America States is < 5/100,000 in males, < 3/100,000 in females and is increasing in the recent three decades as a result of the high prevalence of Hepatitis C^2-4^. HCC commonly develops in a setting of chronic liver cell injury, which leads to inflammation, hepatocyte regeneration, liver matrix remodeling, fibrosis, and ultimately, cirrhosis^5 6^. The major etiologies of liver cirrhosis include chronic hepatitis B virus (HBV) and hepatitis C virus (HCV) infection, alcohol consumption, steatosis, aflatoxin exposure, diabetes, etc. In Asia, HCC is mainly due to chronic HBV infection^5^. Overall, HCC is associated with cirrhosis in about 80% of cases and is currently the leading cause of death among cirrhotic patients^6^.

In order to determine whether locally advanced, metastatic or recurrent HCCs are candidates of systemic treatment, in the last thirty years, many anti-cancer agents or combinations of agents have been tested in HCC, including systemic chemotherapy, immunotherapy and hormonal therapy^7-9^. The clinical application of more aggressive systemic chemotherapy regimens is severely limited by liver cirrhosis and compromised liver function in advanced stage HCC patients. Systematic reviews and meta-analyses consistently demonstrated that systemic chemotherapy did not prolong survival in patients with advanced HCC. The median overall survival (mOS) ranged from 3-7 months in most clinical studies, regardless of different etiology, ethnic group, and standard of care across the regions^7 10 11^.

Two recent randomized Phase III studies in HCC further confirmed limited effectiveness of chemotherapy in advanced HCC. A study conducted in Hong Kong testing doxorubicin versus PIAF (cisplatin, interferon α-2b, fluorouracil, and doxorubicin) combination showed no significant survival benefit (mOS: 8.6 vs 6.83 months, not statistically significant)^12^.Another international study of nolatrexed versus doxorubicin showed less survival benefit of nolatrexed compared to doxorubicin (mOS: 5.2 vs 7.53 months, p< .05)^13^.

Qin et al^14^ conducted a multicenter, open-label, randomized, phase III study in mainland China, Taiwan, Korea, and Thailand involved 371 patients age 18 to 75 years who had locally advanced or metastatic HCC and were ineligible for curative resection or local treatment. They were randomly assigned at a ratio of one to one to receive either FOLFOX4 (n=184) or doxorubicin (n= 187). Although the study did not meet its primary endpoint, the trend toward improved overall survival (OS) with FOLFOX, along with increased progression free survival (PFS) and response rate (RR), suggests that this regimen may confer some benefit to Asian patients, but an OS benefit cannot be concluded from these data^14^.

All-Trans Retinoic Acid (ATRA), a group of structural and functional analogues of vitamin A, exert fundamental effects on the regulation of epithelial cell growth, differentiation, and development^15^. ATRA exert their biological functions primarily by regulating gene expression through two distinct nuclear receptors, retinoic acid receptors and retinoid X receptors, which are both composed of three subtypes (α, β, and γ). Many of ATRA activities on the cellular level have been well characterized and translated to the regulation of processes like differentiation and cell death, which play critical roles in the outcome of malignant transformation of tissues. It is well known that ATRA is one of the strongest and the most thoroughly studied differentiation inducers which could induce differentiation of several types of tumor cells including stem cells. In fact, retinoid-based differentiation therapy of acute promyelocytic leukemia was one of the first successful examples of molecularly targeted treatment strategies. Our previous studies showed that ATRA could induce differentiation of HCC TICs via TS2/AKT pathway and combined treatment with ATRA and cisplatin would improve therapeutic effect, due to elimination of TICs via ATRA-induced differentiation in vivo and in vitro^16 17^. Thus, ATRA could be able to benefit both cancer prevention and cancer treatment in combination with classical chemotherapeutic agents ^18^. So far, there is no report regarding the efficacy and safety of ATRA and FOLFOX in the treatment of extrahepatic metastatic HCCs. Therefore, our hypothesis is that ATRA administration together with FOLFOX will prolong significant survival benefit compared to FOLFOX alone as palliative chemotherapy in advanced hepatocellular carcinoma patients with extrahepatic metastasis.

# Study Objectives

1. To determine whether ATRA + FOLFOX can improve the overall survival, progress-free survival, time to progress, symptomatic progress, and health-related quality of life.
2. To determine the safety of ATRA in the combination with FOLFOX.

# Study Design

This is a multicenter, double-blinded, placebo-controlled, randomized clinical trial in advanced HCC patients with extrahepatic metastasis. Subjects will be randomly assigned to one of the two arms, either ATRA+FOLFOX or FOLFOX alone. Our study has been registered at <http://www.chictr.org.cn> (ID: ChiCTR-IIR-17012916).

**
[figure not shown]
**

After screening for eligibility and signing of informed consent, qualified subjects will be randomized in a 1:1 ratio to receive ATRA+FOLFOX4 (Group A) or Placebo + FOLFOX4 (Group B). Randomization will be stratified by site and treatment assignments will remain blinded throughout the study.

Names of Therapeutic Agents:

- All-trans-Retinoic Acid (ATRA)
- Oxaliplatin (OXA)
- 5-Fluorouracil (5FU)
- Leucovorin (LV)

Mode of Administration:

ATRA+FOLFOX4 (Group A): ATRA 20 mg oral 3 times/day for 3 days prior to the initiation of chemo (FOLFOX4). ATRA will be discontinued at the end of FOLFOX4(OXA 85mg/m2 iv day1, LV 200mg/m2 iv day1 and day 2, 5FU 400mg/m2 iv bolus at hour 2 and then 600 mg/m2 iv over 22 hours on day 1 and day 2, once every 2 weeks) and a total of 6 cycles were performed. Placebo+FOLFOX4 (Group B):The placebo (replacing ATRA) will be given orally 3 times/day for 3 days prior to the chemo. The placebo will then be discontinued at the end of FOLFOX4 and a total of 6 cycles were performed. The follow-up phase began once a patient terminated the treatment phase.

Subjects will be evaluated for tumor response every 4 weeks. Tumor imagine evaluation will be performed by either computerized tomography (CT) scan or MRI. Progression will be determined based on modified RECIST criteria for HCC. Drug therapy will be continued until unacceptable toxicity or disease progression occurs. If investigator determines the subject is benefiting from the blinded study drug and the subject is willing to continue the blinded study drug, the treatment may be continued beyond radiographic progression. Choice of subsequent therapies in case of progressive disease will be at the best discretion of the investigator, which should be beneficial to subjects overall. Subsequent treatments for HCC will be collected in the follow-up period. Requests for un-blinding will only be granted for emergency medical management. Subjects who have discontinued study therapy due to study drug toxicity or any reason other than confirmed tumor progression will continue to have tumor assessments every 4 weeks until documented radiographic tumor progression. All randomized subjects will be followed for overall survival until the required number of events has been reached.

Discontinuation of Subjects from Treatment: subjects must discontinue the investigational agents for any of the following reasons:

1. Withdrawal of informed consent (subject’s decision to withdraw for any reason).
2. Any clinical adverse event (AE), laboratory abnormality or intercurrent illness which,
3. in the opinion of the investigator, indicates that continued participation in the study is not in the best interest of the subject.
4. Pregnancy.
5. Loss of ability to freely provide consent due to either a psychiatric or physical (e.g. infectious disease) illness.
6. Disease progression*

* Note: If investigator determines the subject is benefiting from the blinded study drug (for example: subject may be experiencing symptomatic improvement at the time of documented radiographic progression) and the subject is willing to continue the blinded study drug, the treatment may be continued beyond radiographic progression.

